### Participants

Females aged 18 years or over with newly diagnosed early-stage breast cancer (stages I–III) that have a tumour of size ≥ 10 mm and are oestrogen receptor negative (ER−) as defined by an ER QuickScore/Allred Score ≤ 5 will be eligible to participate in the TIP trial. Exclusion criteria include factors related to slow drug excretion (e.g. poor renal function), drug interactions (e.g. azole-antimycotics) and risk factors for bleeding (e.g. recent major surgery).

### Screening for eligibility

Assessments for patient eligibility to participate in the trial are completed prior to patient randomisation. These include blood biochemistry, liver function tests, baseline tumour assessment as per National Health Service Breast Screening Programme guidelines [52] and histopathological core biopsy including ER/PR receptor status. An electronic screening log is used to record each patient screened for the trial (even if not approached) and whether or not they were recruited.

### Randomisation

Patients will be randomly assigned (1:1) to either the control or intervention arm. Randomisation will be carried out centrally at the Liverpool Cancer Trials Centre (LCTC) based on pre-specified randomisation lists. The sequence of allocations is produced using the Stata package *ralloc* employing permutated block randomisation with block length of 4, 6 and 8. There are no stratification factors to be considered.

### Intervention group

Patients randomised to the intervention arm will receive Rivaroxaban 20 mg once daily for 11–17 days after diagnosis, prior to further treatment in the form of surgery or neo-adjuvant chemotherapy (NAC). Patients with planned NAC consent to undergo a repeat core biopsy once the trial treatment period has been completed.

Rivaroxaban treatment is stopped 24 h (range 18–36 h) prior to surgery or repeat core biopsy before commencing NAC (Figs. 2 and 3). The dose of 20 mg OD was chosen as this is the licenced dose in the UK for the prevention of stroke and systemic embolism in adult patients with non-valvular atrial fibrillation with one or more risk factors [53]. No other concurrent neoadjuvant breast cancer or anticoagulant therapy is permitted.

**Fig. 2 Fig2:**
[figure not shown]
Thrombin Inhibition Preoperatively (TIP) in Early Breast Cancer Trial flow diagram. In this multi-centre study patients are randomised 1:1 20 mg Rivaroxaban once daily (OD): No Treatment. Randomisation is blinded to pathologists, research laboratory staff and data analysts, but not to patients and clinicians

**Fig. 3 Fig3:**
[figure not shown]
TIP Trial Standard Protocol Items: Recommendations for Interventional Trials (SPIRIT) Figure. Abbreviations: mg, milligram; OD, once daily

All patients in the intervention arm will have an alert sticker placed in their notes to ensure that the medical team are aware that the patient has been anticoagulated and take all necessary precautions to minimise bleeding in the event of any residual anticoagulant effect.

Modifications to the rivaroxaban dose are not allowed; the intervention will simply be discontinued upon presentation with unacceptable toxicity.

### Control group

Patients randomised to the control group will not receive any anticoagulant therapy between diagnosis and either surgery or repeat biopsy prior to commencing NAC. They will receive current standard of care.

The use of a blinded placebo plus usual care comparator was considered in trial design but was decided against given the TIP trial has a biological endpoint (Ki67). Clinicians (surgeons or radiologists performing biopsies) are not to be blinded as a safety measure, but laboratory staff and data analysts will be blinded to avoid bias.

### Procedure

Following randomisation, all patients receive a copy of their signed consent form, a patient information sheet and a patient contact card. Residual tissue from the formalin-fixed paraffin-embedded pre-treatment diagnostic core biopsy tissue which is routinely stored will be requested for trial purposes and a 35-ml venous blood sample collected.

Upon termination of Rivaroxaban treatment or none, residual formalin-fixed and fresh tumour tissue will be obtained from trial patients undergoing surgery after routine clinical processing or from the repeat research biopsy prior to NAC.

All post-trial care, including provision for compensation, is through the NHS standard care pathway and NHS channels.

### Patient and public involvement

Patient and public representatives (PPI) were involved in the set-up of the trial, and a patient representative will take part in Trial Steering Committee meetings. PPI indicated to us that the trial risk was minimal and acceptable.

### Measures

Pathologists, research laboratory staff and data analysts will be blinded to patient randomisation in the TIP trial for assessment of both primary and secondary outcome measures.

### Primary outcome measure

#### Ki67

The primary outcome measure of the TIP trial is to determine the absolute and percentage change in the tumour tissue expression of the biomarker Ki67 before and after Rivaroxaban treatment, with the control arm acting as a reference group.

The completely specified primary outcome measure as defined by the five elements set out by Saldanha et al. [54]: *(1) Domain*: Breast cancer tumour cell proliferation. *(2) Specific measurement*: Immunohistochemical assessment of the proportion (%) of cells staining for the nuclear antigen Ki67. *(3) Metric*: Absolute and percentage change from baseline. *(4) Method of aggregation*: Mean. *(5) Time point*: Post-treatment (‘end-of-trial’, 14 days range 11–17, at time of surgical excision or repeat core biopsy prior to neoadjuvant chemotherapy).

### Secondary outcome measures

A range of potential breast cancer pharmacodynamic biomarkers will be studied as secondary outcome measures:
Primary mammosphere formation assays will be performed ex vivo on fresh tumour tissue at the end-of-trial time-point to determine cancer stem cell activity. This data will be presented as a comparison of the means of mammosphere forming efficiency (MFE) in the intervention and control arms. MFE is calculated by dividing the number of mammospheres formed at 7 days by the number of cells seeded [55].Formalin-fixed paraffin-embedded (FFPE) tissue will be assessed for tumour markers of angiogenesis (CD31), apoptosis (Cleaved caspase 3, TUNEL) and the extrinsic clotting pathway (Tissue Factor, thrombin, PAR-1; in both epithelial cells/fibroblasts) by immunohistochemistry. Baseline core biopsy samples and end-of-trial biopsy samples will be assessed, and mean values analysed.Plasma biomarkers of coagulation (Tissue Factor, thrombin and d-dimer) will be quantified by enzyme-linked immunosorbent assay (ELISA) with the change from baseline to the end-of-trial time-point assessed. Mean biomarker will be compared between the control and intervention arms.FFPE tissue and plasma will be stored for future translational research, for example ctDNA, with patient consent.

Trial tumour tissue, plasma and serum samples, both for short-term storage and for future translational research, will be stored in temperature-controlled facilities at the Oglesby Cancer Research Building in Manchester, UK. This patient material will all be stored according to Good Clinical Laboratory Practise (GCLP) guidelines [56].

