### Study design

The TIP trial is a phase II preoperative window-of-opportunity randomised controlled trial of Rivaroxaban compared to no treatment in ER-negative stage I–III early breast cancer patients.

This UK-based multi-centre study will randomise 88 eligible patients (1:1) to either Rivaroxaban 20 mg once daily (OD) or no treatment (control). Randomisation will be blinded to pathologists and data analysts, but not to patients or clinicians.

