### Sample size calculation

The trial is designed with a two-sided alpha level of 0.05 and an estimated 80% power to detect a 0.6 standard deviation (SD) reduction in percentage tissue expression of Ki67 in early breast cancer patients treated with Rivaroxaban. Based on a two-sample *t* test with this 80% power, 88 eligible patients are required. We will allow for a 10% drop out rate, and therefore, 8 extra patients (giving a total of 96 patients) may need to be recruited. Any patient that withdraws from the trial or does not have surgery or a repeat core biopsy following treatment will be removed from the study and replaced.

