#### Ki67

Manual Section Score Ki67 will be compared between arms using a beta regression model including terms accounting for baseline Ki67, treatment arm, and covariates known to be associated with Ki67 such as tumour grade and HER-2 status. Although the sample size is based on a *t* test, a beta regression model for the analysis is superior, partly because the analysis would be on the original scale, partly because covariates including baseline would be easily accounted for and partly because treatment effects on variance could be explicitly modelled. Ki67 measurements will be performed in accordance with national guidance [57].

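### Secondary tissue and plasma markers with a baseline value are described as compared by means or change, with no baseline term stated, which is less precise than the adjustment used for Ki67

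*Protocol article*

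**What the plan says.** All references are to the protocol article.

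- **Tissue markers** (Secondary outcome measures). CD31, cleaved caspase 3, TUNEL, Tissue Factor, thrombin and PAR-1 are measured by immunohistochemistry: "Baseline core biopsy samples and end-of-trial biopsy samples will be assessed, and mean values analysed".
- **Plasma markers** (same section). Tissue Factor, thrombin and d-dimer are measured by ELISA, "with the change from baseline to the end-of-trial time-point assessed". The next sentence reads "Mean biomarker will be compared between the control and intervention arms".
- **Mammosphere forming efficiency** (same section). This is measured at the end of the trial only, so it has no baseline.
- **Analysis**. For the secondary outcomes this section adds intention to treat and the handling of missing data. It gives no model.
- **Ki67** (under Analysis). The primary outcome is analysed by beta regression with baseline Ki67, arm and covariates. The model is preferred to the t test "partly because covariates including baseline would be easily accounted for", among other reasons.

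**The concern.** Every tissue and plasma marker in the list has a value at both times. The article recognises for Ki67 that a baseline should enter the model, but for the secondary markers it describes only means or change.

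Neither quantity uses the baseline efficiently. An end-of-trial mean ignores it. A change score subtracts all of it, which over-corrects when the two measurements are only moderately correlated. The plasma wording also leaves open whether mean change or the end-of-trial mean is compared between arms, and the two can differ in the same data.

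What is at stake is precision on the mechanistic outcomes that will be used to interpret the Ki67 result. Intervals would be wider than they need be in a trial of 44 per arm.

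**Working it through.** **1. The plan's own figure.** Sample size calculation: "two-sided alpha level of 0.05 and an estimated 80% power to detect a 0.6 standard deviation (SD) reduction", and "88 eligible patients are required" by a two-sample t test. Allocation is 1:1 (Study design). By the normal approximation:

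n per arm = 2 × (1.960 + 0.842)² / 0.6² = 43.6, rounded up to 44, or 88 in total.

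Power at 44 per arm is 80.4% by this approximation and 79.5% by the exact t test. The figure reproduces. It is stated for Ki67 only; the 0.6 SD is borrowed below as an illustration.

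**2. Inputs for the comparison.** Let rho be the correlation between baseline and end-of-trial values of a marker. The article gives no value, so 0.3 to 0.7 is assumed, with equal SDs at both times and the same rho in both arms.

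**3. Variance of the between-arm difference**, relative to end-of-trial means:

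- end-of-trial means: 1
- change from baseline: 2(1 − rho)
- baseline-adjusted: 1 − rho²

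The ratio of adjusted to change is (1 − rho²) / [2(1 − rho)] = (1 + rho)/2.

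| rho | End-of-trial | Change | Adjusted | Saving against change | Saving against end-of-trial |
|---|---|---|---|---|---|
| 0.3 | 1.00 | 1.40 | 0.91 | 35% | 9% |
| 0.5 | 1.00 | 1.00 | 0.75 | 25% | 25% |
| 0.7 | 1.00 | 0.60 | 0.51 | 15% | 49% |

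Both 1 − rho² and (1 + rho)/2 are below 1 for every rho strictly between 0 and 1, so adjustment beats both alternatives throughout. This ignores the small cost of estimating one more coefficient. Below rho = 0.5, change scores are less precise than end-of-trial means.

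**4. The same in power and patients**, for a 0.6 SD difference (normal approximation). Each cell gives power at 44 per arm, then total N for 80% power.

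| rho | End-of-trial | Change | Adjusted |
|---|---|---|---|
| 0.3 | 80.4%, 88 | 66.2%, 124 | 83.9%, 80 |
| 0.5 | 80.4%, 88 | 80.4%, 88 | 90.1%, 66 |
| 0.7 | 80.4%, 88 | 95.3%, 54 | 97.6%, 46 |

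**5. Where the loss comes from.** Randomisation is unstratified (Randomisation section). At 44 per arm the standardised baseline difference on one marker has standard error √(2/44) = 0.21, so about 5% of trials exceed 1.96 × 0.213 = 0.42 SD in one direction or the other. Given an imbalance of 0.42 SD and rho = 0.5, the end-of-trial contrast is shifted by 0.5 × 0.42 = 0.21 SD and the change contrast by (0.5 − 1) × 0.42 = −0.21 SD. Adjustment removes this shift. Averaged over randomisations the shift is zero, and the unadjusted standard error already allows for it. It is the source of the extra variance in step 3, not a separate harm.

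**The case against.** The strongest reply is that Secondary outcome measures defines outcomes and does not fix an estimator. The Primary outcome measure section also describes Ki67 as change from baseline aggregated by the mean, yet the Ki67 subsection then adjusts for baseline. Similar words for the secondary markers need not exclude adjustment, and a comparison of mean biomarker levels could be of adjusted means. Models for secondary markers are commonly left to an analysis plan, which is not shown here.

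Much of this stands. The tissue wording is loose, and a reader might infer that the plan rules out baseline adjustment; the article does not say so. But the Ki67 subsection replaces the language of means and change for Ki67 alone. For the other markers the article names means and change as the quantities to analyse, and a statistician following it as written would run the less precise comparison. That makes this a point about a described method and not only about silence.

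It is also fair that the size depends on an unknown rho. At rho = 0.2 the saving against end-of-trial means is 1 − 0.96 = 4%, and at high rho the saving against change scores is small.

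A reader might also infer that unadjusted comparisons could mislead about the direction of effect. That would be chance error, which a valid confidence interval already covers.

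**Conclusion.** The point holds as one of efficiency on secondary outcomes. As described, the tissue and plasma comparisons are unbiased under randomisation but less precise than a baseline-adjusted comparison for any rho strictly between 0 and 1. For assumed rho of 0.3 to 0.7 and equal SDs, the variance saving is 15% to 35% against change scores and 9% to 49% against end-of-trial means. The direction is certain in that range; the size rests on rho, which the article does not give.

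A reader might take this as a flaw in validity or in the power of the trial. The documents do not support that: the power statement concerns Ki67, the Ki67 model already contains baseline, and neither the primary analysis nor the 88 patients is affected.

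**What to change.** In Secondary outcome measures, or in the analysis plan before the data are analysed, state that each secondary marker with a baseline is compared between arms by regressing its end-of-trial value on arm and baseline value, and that the adjusted difference or ratio is reported with a 95% confidence interval.

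Choose the scale marker by marker. The article does not say whether the tissue markers are scored as percentages, counts or ordinal scores, or how the plasma values are distributed, so one scale or model should not be imposed on all of them. If a proportion model is used, say how exact zeros are handled, because standard beta regression does not accept them.

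Mammosphere forming efficiency has no baseline and stays as planned.

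The cost is wording. No extra patients, samples or assays are needed.

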### Analysis

Both primary and secondary analyses will be carried out on an intention to treat (ITT) basis. Missing data or missing patients’ samples will be minimised by active monitoring by the Trial Coordinator, regularly reviewed by the Trial Management Group (TMG), including scheduled data cleaning, sample checking and communications with trial sites. If samples for the primary endpoint analysis are not collected, the patient will be replaced. Any patients who withdraw from the trial will be replaced. If the level of missing data exceeds these safeguards, it may be handled by multiple imputation. Separate multiple imputations by treatment arm would be performed, using the method of chained equations.

#### Ki67

Manual Section Score Ki67 will be compared between arms using a beta regression model including terms accounting for baseline Ki67, treatment arm, and covariates known to be associated with Ki67 such as tumour grade and HER-2 status. Although the sample size is based on a *t* test, a beta regression model for the analysis is superior, partly because the analysis would be on the original scale, partly because covariates including baseline would be easily accounted for and partly because treatment effects on variance could be explicitly modelled. Ki67 measurements will be performed in accordance with national guidance [57].

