The trial was initially designed as a window-of-opportunity pre-surgery study; however, with changing clinical practice, increasingly ER-negative patients are having neoadjuvant chemotherapy. Therefore, an amendment to the study was submitted to allow inclusion of neoadjuvant patients, with the post-trial biopsy being an additional research biopsy. It is routine to undergo radiological clip placement prior to commencement of chemotherapy, to allow identification of the tumour bed in the presence of complete radiological response to NAC. Therefore, to minimise impact on trial patients, the post-trial biopsy is performed at the time of clip placement. This was assessed as acceptable by our patient and public collaborators.

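### Planned pathway (excision versus repeat core) is neither stratified for nor a named covariate, which leaves avoidable noise in the primary Ki67 comparison

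*Protocol article*

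**What the plan says.** The Procedure section of the protocol article takes baseline tissue from the stored diagnostic core for every patient. The Aim, Procedure and Primary outcome measure sections place the end-of-trial reading at surgical excision or, before NAC, at a repeat core biopsy. The Intervention group section says that patients with planned NAC consent to the repeat biopsy, so their pathway is foreseeable at consent. The Discussion explains how the second pathway arose: "an amendment to the study was submitted to allow inclusion of neoadjuvant patients, with the post-trial biopsy being an additional research biopsy". It gives increasing use of NAC in ER-negative patients as the reason.

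On allocation, the Randomisation section states "There are no stratification factors to be considered". On the model, the Ki67 part of the Analysis section specifies a beta regression with baseline Ki67, treatment arm and "covariates known to be associated with Ki67 such as tumour grade and HER-2 status". Neither pathway nor specimen type is named there, and the article describes no analysis by pathway.

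**The concern.** Change from baseline means core-to-excision in one pathway and core-to-core in the other. If Ki67 reads systematically higher or lower on an excision than on a core, the baseline term cannot absorb that shift, because every baseline reading is a core. Grade and HER-2 may absorb part of a difference in the kind of patient on each pathway, but not a difference due to the specimen. The measurement safeguards that the article describes (blinded reading, staining in a single batch) do not address specimen type either.

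With pathway neither stratified for nor in the model, a shift does two connected things. It adds to the residual variance, and in any one randomisation it moves the estimated treatment difference by the shift multiplied by the chance imbalance in pathway share. In a trial of 88 patients with power of about 80%, there is little precision to spare. Planned pathway is a pre-randomisation characteristic that could be adjusted for at almost no cost.

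**Working it through.** **Inputs from the Sample size calculation section:** two-sided alpha 0.05; "an estimated 80% power"; an effect of 0.6 SD; "88 eligible patients are required", which is 44 per arm at 1:1.

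**Assumed, because the article gives neither:** the share p of patients on the repeat-core pathway (30% and 50%), and the pathway shift s in end-of-trial Ki67, in within-pathway SDs (0.3, 0.5 and 1.0).

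**1. The plan's own figure.** Normal approximation: n per arm = 2(1.96 + 0.842)²/0.6² = 43.6, rounded up to 44, total 88. This matches the plan. The exact noncentral t gives 79.5% power at 44 per arm, and that is the reference value below.

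**2. Chance imbalance in pathway.** The SD of the between-arm difference in pathway share is √(2p(1−p)/44).
- p = 0.3: √(0.42/44) = 0.098; 95% limits about ±19 percentage points.
- p = 0.5: √(0.50/44) = 0.107; 95% limits about ±21 points.

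The movement in the treatment difference is s × imbalance. At p = 0.5:

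| s | at 1 SD of imbalance | share of 0.6 SD | at the 95% limit | share of 0.6 SD |
|---|---|---|---|---|
| 0.3 | 0.03 SD | 5% | 0.06 SD | 10% |
| 0.5 | 0.05 SD | 9% | 0.10 SD | 17% |
| 1.0 | 0.11 SD | 18% | 0.21 SD | 35% |

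**3. Power with pathway ignored.** If 0.6 SD is a within-pathway SD, the total SD is √(1 + s²p(1−p)) and the effective standardised difference is 0.6 divided by that. For s = 0.5 and p = 0.5: √1.0625 = 1.031, and 0.6/1.031 = 0.582. Noncentral t, 44 per arm, no covariates:

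| s | p = 0.3 | p = 0.5 |
|---|---|---|
| 0 | 79.5% | 79.5% |
| 0.3 | 78.7% | 78.6% |
| 0.5 | 77.4% | 77.0% |
| 1.0 | 71.6% | 70.2% |

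**4. With baseline Ki67 in the model.** As an illustration, assume a within-pathway baseline correlation of 0.5. The residual variance is then 0.75 + s²p(1−p). At p = 0.5 and s = 0, 0.6/√0.75 = 0.693 gives 89.5% power. With s = 0.5, 0.6/√0.8125 = 0.666 gives 87.0%. With s = 1.0, the residual variance is 1.0 and power is 79.5%. The baseline term raises power throughout, but the loss from ignoring pathway remains: 2.5 points at s = 0.5 and 10 points at s = 1.0.

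Steps 2 and 3 describe the same phenomenon. The variance in step 3 already contains the imbalance in step 2, so the two must not be added together.

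**The case against.** Much of the case on the other side stands.

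- **The covariate list is open.** Grade and HER-2 are given as examples, and the final list may be in a full protocol or analysis plan that is not shown. A reader might infer that pathway is excluded from the model; the article does not say so. However, the stated criterion is association with Ki67, illustrated only by tumour features, and it does not clearly reach a feature of the measurement. The lack of stratification is stated outright.
- **Unstratified allocation is legitimate.** Blocked 1:1 allocation with covariate adjustment is an acceptable design at this size. It is not an error in itself.
- **The sizes are assumed.** The article does not report that core and excision readings differ. If 0.6 SD is the overall SD, 88 patients give the planned power with pathway ignored, and adjustment would be a gain over the plan.
- **The t test is not the planned analysis.** The planned model includes baseline Ki67, and step 4 shows that power may still exceed 80% with a shift of 0.5 SD.

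Two further inferences are tempting but unsupported. One is that the amendment changed the outcome specimen while randomisation and model went unrevised: no pre-amendment text is shown, so what was or was not revised is unknown. The other is that planned pathway is already in the data: the consent arrangement makes it foreseeable, but nothing in the article says that it is recorded before randomisation.

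**Conclusion.** The point holds as a matter of precision. The primary endpoint mixes two end-of-trial specimen types, allocation is unstratified, and the covariates named do not remove a specimen shift. Under the stated assumptions (30–50% NAC share, 0.6 SD as within-pathway SD, unadjusted t test with 44 per arm), ignoring pathway costs about 1 to 2.5 points of power for shifts of 0.3–0.5 SD and about 8 to 9 points for 1.0 SD. Power is higher throughout once a correlated baseline is in the model. If the true shift is small, the loss is negligible.

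A reader might take the mixed specimens to mean that the treatment comparison is biased or its type I error inflated. The article does not support that. Allocation is random with respect to planned pathway, so imbalance arises only by chance, and an unadjusted standard error already allows for it. The case for acting rests on the very low cost of the remedy and on settling the adjustment before outcome data are seen.

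**What to change.** In the Ki67 analysis text, name planned pathway (surgery versus repeat core before NAC), as determined before randomisation, as a fixed covariate in the beta regression. Use the planned and not the actual pathway, so that the model does not condition on something that happens after allocation. Report Ki67 by pathway and arm as a supportive summary.

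The cost is one model term, plus confirmation that planned pathway is captured at or before randomisation. The sample size stays at 88. If recruitment is still open, the remaining allocation could also be stratified by the same variable. That would need a new list at the trials unit and is optional, since the covariate deals with most of the problem.
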